### Strategies to improve adherence to intervention {11c}

The drug is taken under the supervision of a nurse in hospitalized patients. The amount of medication used in the out-patient setting is regularly checked, just by history taking, at each chemotherapy visit by the treatment team. Also, a member of the research team checks the regular use of the drug at least once by phone between every two visits of the patients.

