#### Allocation concealment mechanism {16b}

The sealed, opaque, and sequentially numbered envelopes prepared by an epidemiologist along with packages containing 30 tablets in groups A and B are provided to the treating physicians without specifying which is the drug or the placebo. The content of each random envelop identifies patients’ group, A or B.

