#### Plans to promote participant retention and complete follow-up {18b}

Monitoring of patients’ compliance in the study is done in such a way that these patients are either hospitalized or visit every 2 to 3 weeks and therefore are regularly supervised. At the same time, the patient does not have to stay in the study and also does not need to provide any reason to leave it. Explanations are given to the patient about the safety of the drug and additional care that the research team provides would increase patients’ cooperation. There will be no outcome data collected for participants who discontinue or deviate from intervention protocols.

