#### Methods of analyses to handle protocol non-adherence and statistical methods to handle missing data {20c}

The analysis is based on per-protocol and any dropout or group crossing will be excluded from the final analysis. The probable missing data will not be imputed.

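### Out-patient intake is known only from patient report, yet the only analysis named is per-protocol and outcomes are not collected after deviation, so self-report may affect who is analysed

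*Protocol article*

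**What the plan says.** Section {11c} sets two standards of adherence measurement. For in-patients: "The drug is taken under the supervision of a nurse in hospitalized patients". For out-patients: "The amount of medication used in the out-patient setting is regularly checked, just by history taking", which the treatment team does at chemotherapy visits. The one further check is a call: "a member of the research team checks the regular use of the drug at least once by phone between every two visits of the patients".

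Section {20c}, which covers non-adherence and missing data, says: "The analysis is based on per-protocol and any dropout or group crossing will be excluded from the final analysis". It adds: "The probable missing data will not be imputed". No analysis of all randomised patients is named. Section {18b} says: "There will be no outcome data collected for participants who discontinue or deviate from intervention protocols".

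Section {16b} describes "packages containing 30 tablets in groups A and B", and section {16c} has the treating physician hand the matching package to the patient. By section {18b}, patients are either in hospital or seen every two to three weeks.

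**The concern.** Limiting the out-patient check to history taking is a stated choice, not a detail lost in condensing the protocol. In a trial that analysed everyone as randomised, it would be a modest weakness in a supportive variable. Here it sits beside a per-protocol analysis and a rule that ends outcome collection after deviation.

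An out-patient who admits missed doses might be treated as having deviated, and then have no outcome and no place in the analysis. An out-patient who missed as many doses but did not say so would stay in. In-patients are not exposed to this error in the same way.

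The error need not be random. The Limitations section expects intolerance of the drug in patients with nausea and vomiting around chemotherapy, and section {11a} gives gastrointestinal intolerance as one reason for the dose. If tolerability differs between drug and placebo, missed doses and the admission of them may differ by arm. Selection on them would then weaken the protection that randomisation gives.

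**Working it through.** **1. Does the pack allow a count?**

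Inputs: 30 tablets per package ({16b}); one tablet every other day ({11a}); duration given as 2 months and also as 8 weeks (both in {11a}); visits every two to three weeks ({18b}). I take 2 months as 60 days.

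Tablets due = days / 2.

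| Time point | Tablets due | Left of 30 if all taken |
|---|---|---|
| Day 14 | 14 / 2 = 7 | 23 |
| Day 21 | 21 / 2 = 10.5, so 10 or 11 | 20 or 19 |
| 8 weeks (56 days) | 56 / 2 = 28 | 2 |
| 2 months (60 days) | 60 / 2 = 30 | 0 |

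The pack size is reproduced from the 2-month duration. One pack covers the whole course under either duration, so a count fits into existing visits. The two durations give different expected totals (30 and 28), so the passages must be reconciled before a share taken can be computed.

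**2. How could patient report reach the analysis set?**

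- {11c}: for out-patients, the only information on intake is what the patient says, at visits and by phone.
- {20c}: the analysis is per-protocol. The exclusions named are dropout and group crossing. Missed doses are not named and no threshold of intake is given.
- {18b}: outcome collection ends for those who discontinue or deviate from the intervention. This is broader than the two exclusions in {20c} and can be read to include missed doses, but it does not say so.

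So the path exists only through {18b} and through the term per-protocol under a heading on non-adherence. It is an inference, and it applies to out-patients only.

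**3. Can the effect be sized?**

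That would need the out-patient share, reported and true intake by arm, and the rule that turns missed doses into deviation. The article gives none of these, so no figure is offered.

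**4. What can still be changed?**

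Recruitment ended in January 2021 ({15}), and the status date is 26 March 2021 (Trial status). Assume the last patient started on 31 January. Then 56 days of treatment end on 28 March and 60 days on 1 April. Counts during treatment were therefore nearly or wholly out of reach at the status date. Section {20a} still writes of the data analysis in the future tense.

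**The case against.** The strongest reply is that {20c} lists its exclusions and self-reported missed doses are not among them. The share of doses that defines a per-protocol set is also commonly left to the statistical analysis plan, which is not shown. Both points stand. A reader might infer that patients who admit missed doses will be excluded; the text does not say that, and the absence of a threshold from the article is not itself a fault. What remains is that {18b} uses the wider term deviation and attaches loss of outcome data to it.

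A reader might also infer that the whole analysis set rests on self-report. It does not: in-patient doses are supervised, acute leukaemias and high-grade lymphomas are included, and recruitment covers in-patient wards. Nor does the article say that breast and colon patients are mainly out-patients.

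It is tempting to express the problem as a diluted treatment effect with a larger sample needed. That would measure tablets not taken. Such dilution occurs whether intake is asked about or counted, and it remains in an all-randomised comparison.

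It is equally tempting to say that history taking is what would make a null result uninterpretable. By section {14}, incidence is 1 to 8% with 30 patients per group, so the control group would expect 30 x 0.01 = 0.3 to 30 x 0.08 = 2.4 cases. A null result would say little even with perfectly measured intake. Sample size is a separate matter.

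Finally, a count is imperfect. A vomited or discarded tablet is missing from the pack and counts as taken, whereas asking the patient can reveal it. This argues for count and history together.

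**Conclusion.** The point holds in a limited form. Out-patient intake is known only from patient report, the only analysis named is per-protocol, and outcomes are not collected after deviation. To the extent that missed doses are treated as deviation, self-report can affect which out-patients have outcomes and are analysed, possibly in relation to tolerability. This rests on reading deviation in {18b} as including missed doses, which is plausible but unstated. Neither the size nor the direction of any bias can be obtained from the article. A tablet count would improve the measurement but would not cure a per-protocol-only analysis, so the choice of analysis set matters more and is also the part most clearly still open to change.

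**What to change.** 1. Make the comparison of all randomised patients, in their assigned groups, the main analysis. Keep collecting outcomes after discontinuation or deviation, or recover them where follow-up has ended. Use the per-protocol set only as supportive.
2. Where packs are still available, count the tablets left in the 30-tablet pack at existing visits and at the end of treatment, and record tablets taken over tablets due beside the history. Reconcile the 2-month and 8-week statements so that there is one expected number. Fix the adherence share that defines the per-protocol set before the code is opened.
3. If counts can no longer be made, report out-patient adherence as self-reported.

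Cost: item 1 requires an amended analysis section and effort to trace outcomes. Item 2 takes about a minute per visit and patients must bring the pack. Because discarded or vomited tablets still count as taken, keep history taking alongside the count. Item 3 costs a sentence in the report.

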### Relevant concomitant care permitted or prohibited during the trial {11d}

All patients must adhere to prevention procedures such as hand hygiene, face mask, social distancing, and isolation throughout the study period.

### Provision for post-trial care {30}

All researchers in this study have occupational liability insurance according to legal requirements in Iran. This insurance will cover all the costs of damages to the patient due to medical malpractice up to 5 years after its occurrence.

### Outcome {12}

The primary endpoint is the comparison of the COVID-19 incidence in the two groups of study. Patients are assessed for the outcome for the entire duration of 8 weeks of drug use and up to 2 weeks after stopping the drug. The secondary endpoint is to evaluate disease severity in both arms. Criteria used to assess disease severity include clinical and paraclinical. Clinically, what shows the severity of the disease is the degree of dyspnea and decreased arterial oxygen saturation. The amount of supplemental oxygen required by the patient and the method of its administration, i.e., the type of mask and invasive or non-invasive ventilation, are also recorded. The best paraclinical criterion for determining the severity of the disease in cancer patients is the extent of pulmonary involvement on lung HRCT scan. Other factors that help include lymphopenia, the rate of increase in inflammatory markers, the length of hospital stay, and the rate of intensive care unit (ICU) stay.

### Participant timeline {13}

Table 1 shows the participant timeline.

**Table 1 Tab1:**
[figure not shown]
Participant timeline

*Serologic testing consists of SARS-CoV-2-specific antibody by ELISA method

^#^Hydroxychloroquine

The schedule presented in Table 1 was designed from the beginning, but due to the events that occurred, which are described in section {15}, the timeline was extended, the course of which is mentioned in the section {15}.

### Sample size {14}

We considered an assumption of about 40% decrease in the incidence of COVID-19 in cancer patients by administering HCQ. The incidence of COVID-19 in the cancer population has been reported in studies between 1 and 8% [27, 28]. Using the formula for comparing two proportions in G-power version 3.1.9.7 [29], and an alpha error of 0.05, power of 80%, and an allocation ratio of 1:1, the required sample size in each group was estimated as 30 individuals.

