**Trial design:**

This is a two-arm, parallel-group, triple-blind, phase 2–3 randomized controlled trial.

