**Sample size:**

The calculated total sample size is 60 patients, with 30 patients in each group.

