### Statistical methods

#### Statistical methods for analyzing primary and secondary outcomes {20a}

Data analysis will be performed using SPSS software version 16 (SPSS Inc., Chicago, IL, USA). Quantitative variables will be described by mean and standard deviation and qualitative variables will be described by frequency and percentage. Quantitative variables between control and intervention groups will be compared by Student’s *T*-test or Mann-Whitney test.

The comparison of qualitative variables between the two groups will be performed by the chi-square test and Fisher’s exact test. For intragroup comparisons, paired *T*-test or Wilcoxon test will be used. All tests will be two-tailed and the significant level will be considered less than 0.05.

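### The sample size of 30 per group and the 80% power do not follow from the stated inputs: the best stated case needs about 918 per group, and 30 per group gives roughly 1% to 7% power

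*Protocol article*

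**What the plan says.** All the ingredients of the calculation stand in the protocol article.

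- Effect, Sample size {14}: "We considered an assumption of about 40% decrease in the incidence of COVID-19 in cancer patients by administering HCQ".
- Control incidence, same section: "The incidence of COVID-19 in the cancer population has been reported in studies between 1 and 8" per cent. No single design value is chosen from the range, and the period it refers to is not given.
- Method, same section: "Using the formula for comparing two proportions in G-power version 3.1.9.7".
- Error rates, same section: "an alpha error of 0.05, power of 80%, and an allocation ratio of 1:1".
- Sidedness, Statistical methods {20a}: "All tests will be two-tailed and the significant level will be considered less than 0.05". The same section names the chi-square and Fisher's exact tests for qualitative variables, which covers the binary primary endpoint.
- Result, Sample size {14}: "the required sample size in each group was estimated as 30 individuals". The abstract repeats it: "The calculated total sample size is 60 patients, with 30 patients in each group".

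The abstract describes the study as a "phase 2–3 randomized controlled trial". Outcome {12} makes the comparison of COVID-19 incidence between the arms the primary endpoint, over 8 weeks of treatment plus 2 weeks.

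**The concern.** An incidence of at most 8% gives at most two or three cases among 30 control patients. A 40% reduction in so few cases cannot be detected with 80% power, so the stated output looked incompatible with the stated inputs.

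The power claim is the only justification given for enrolling 60 patients. If it is false, a non-significant primary result is close to certain under the plan's own assumptions, whether or not the drug has the assumed effect. A reader who trusts the 80% figure could then take that result as evidence against a 40% reduction, when the data could not have shown one.

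**Working it through.** **Inputs.** Control risk p1 = 0.01 to 0.08 and a 40% decrease ({14}); two-sided alpha 0.05 ({14}, {20a}), so z = 1.960; power 80% ({14}), so z = 0.842; equal groups ({14}).

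**Readings of the 40% decrease.** As an absolute difference it would give a negative risk (0.08 − 0.40), so it can only be relative: p2 = 0.6 × p1.

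**Attempt to reproduce the figure of 30.** The pooled two-proportion formula, with p̄ = (p1 + p2)/2, is

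n per group = [1.960·√(2p̄(1−p̄)) + 0.842·√(p1(1−p1) + p2(1−p2))]² / (p1 − p2)²

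- 8% against 4.8%: (0.6784 + 0.2907)² / 0.032² = 0.93915 / 0.001024 = 917.1, so **918**.
- 4% against 2.4%: 0.48595 / 0.000256 = 1,898.2, so **1,899**.
- 1% against 0.6%: 0.12456 / 0.000016 = 7,784.9, so **7,785**.

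The stated 30 is too small by a factor of about 31 (918/30) to 260 (7,785/30).

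**Variants tried at 8% against 4.8%.** Continuity-corrected 979; arcsine 905; unpooled variance 915; one-sided 723, which {20a} rules out in any case. None comes near 30. Total prevention (8% against 0) still needs 0.59519 / 0.0064 = 93.0, so 93.

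**What would give 30.** A 40% relative decrease needs about 30 per group only when the control risk is near 84% (84% against 50.4% gives 29.4, so 30). Treating 40% as a control incidence and 8% as the treated incidence gives 27 by this formula, 33 with continuity correction and 31 by exact Fisher power. That is an 80% relative reduction and contradicts both the stated incidence and the stated effect. Other pairs also give about 30, so the document does not show how the figure arose.

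**Power at 30 per group.** Normal approximation at 8% against 4.8%: Φ[(0.032·√30 − 0.6784)/0.3454] = Φ(−1.457) = 7.3%. Exact power sums the product of the two binomial probabilities over every pair of case counts with p < 0.05.

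| Control vs treated risk | Expected cases | Fisher | Uncorrected chi-square |
|---|---|---|---|
| 8% vs 4.8% | 2.4 vs 1.44 | 0.8% | 6.5% |
| 1% vs 0.6% | 0.3 vs 0.18 | below 0.001% | 0.02% |
| 8% vs 0 | 2.4 vs 0 | 2.9% | 21.6% |

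When the treated arm has no cases, Fisher's test needs six in the control arm: 5 against 0 gives p = 0.052 and 6 against 0 gives p = 0.024. At 1% against 0.6% the probability of no case in either arm is 0.99³⁰ × 0.994³⁰ = 0.62. For Fisher's test to reach about 80% power when the drug prevents every case, the control risk must be about 25%.

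**Losses.** Eligibility {10}, {11b} and {20c} exclude infections in the first two weeks, patients with side effects, dropouts and crossovers. Sample size {14} mentions no allowance for these. They lower the numbers further, though little beside a thirty-fold shortfall.

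**The case against.** The best counter-argument is that the 1% to 8% is a literature range, not a forecast for this trial. Study setting {9} enrols a high-risk haematological group, and {11a} also counts typical symptoms with three negative PCR tests as COVID-19, so incidence in the trial could exceed 8%. That is possible, but {14} states no higher rate, and a higher rate would have to be very much higher to help: at 20% against 12%, power with 30 per group is still only about 6% (Fisher) to 13% (chi-square). The point does mean that the power figures here are conditional on the inputs in {14}.

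Several further objections stand in part. The document does not say how a null result will be interpreted, so a misreading is a risk and not something the plan states. The phase label is not derived from the power calculation, so changing it is a consequence to consider and not part of the arithmetic error. A full protocol could hold a dropout allowance, and details of interval estimation could sit in an analysis plan that is not shown. None of this touches the core: {14} gives a complete calculation, and no fuller document could reconcile it without replacing one of its inputs.

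**Conclusion.** The concern holds. With the article's own inputs, 80% power needs at least 918 per group, not 30. The best power that 30 per group offers against the assumed effect is 0.8% (Fisher), 6.5% (exact chi-square) or 7.3% (normal approximation). Lower in the stated range it is practically zero by exact calculation.

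This rests on reading the 40% as relative, which is the only possible reading, on the two-sided 0.05 level in {20a}, and on 8% as the upper limit of control incidence. It assumes all 30 patients per group are analysed, which favours the plan. The trial as sized cannot answer its primary question in the way claimed, and the sample size statement must be corrected.

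**What to change.** Recruitment {15} and Trial status report that recruitment is over, so the correction is to the justification and to the reporting.

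- In {14} and the abstract, withdraw the statement that 30 per group follows from an 80% power calculation. If other inputs were actually used, state them and their source.
- State the achieved power: at 8% against 4.8%, about 0.8% by Fisher's test and 6.5% by the uncorrected chi-square test. State also what 30 per group could detect, for example that total prevention reaches about 80% power by Fisher's test only at a control incidence of about 25%.
- In {8} and the abstract, describe the trial as a pilot or estimation study in place of the phase 2–3 label.
- Make the risk difference and risk ratio, with exact or score 95% confidence intervals, the main result. For illustration, 2 control cases against 1 treated case gives a risk ratio of 0.50 with a score interval of about 0.07 to 3.65.
- State that p above 0.05 will not be read as absence of effect. If the analysis has not begun, record this beforehand; otherwise report it openly as a later clarification.

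The cost is a rewording of {14}, {8} and the abstract and a short addition to {20a}. No further patients or data are needed. The price is that the stated power becomes unfavourable.

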### Recruitment {15}

Patients will be recruited from individuals referred to out-patient oncology clinics and in-patient hematology-oncology wards of Ghaem and Imam Reza hospitals, Mashhad, the tertiary and referral centers of hematology and oncology in the east of Iran.

Patients are selected based on inclusion and exclusion criteria by treating physicians and researchers.

Recruitment of this study began in May 2020. Unfortunately, in less than 3 weeks from the start of work in May 2020, recruitment was stopped following the publication of an article against hydroxychloroquine in *The Lancet* journal and WHO statement. Our study was completely stopped for 6 weeks. After retracting the study in *The Lancet* journal, we were able to resume work. Because the results of many studies on hydroxychloroquine were published on those days and often did not support the effect of this drug in treating COVID-19 [30], our recruitment process continued very slowly. Recruitment finally ended in January 2021.

The reason why our study continued after these events was that, according to the WHO recommendation, hydroxychloroquine was excluded from COVID-19 treatment but could be used for prevention in most clinical trial studies [31].

### Assignment of interventions: allocation

#### Sequence generation {16a}

The randomization method was performed base on permuted block randomization. Using the website http://randomization.com/, a random sequence is generated using quadruple blocks.

#### Allocation concealment mechanism {16b}

The sealed, opaque, and sequentially numbered envelopes prepared by an epidemiologist along with packages containing 30 tablets in groups A and B are provided to the treating physicians without specifying which is the drug or the placebo. The content of each random envelop identifies patients’ group, A or B.

#### Implementation {16c}

An epidemiologist will generate an allocation sequence. The treating physician who is blind about the groups selects the first envelope for the first patient and gives the corresponding pill package to the patient.

### Assignment of interventions: blinding

#### Who will be blinded? {17a}

This study is a triple-blind study. The intervention arm is unknown to patients, treating physicians, researchers, and analyzers.

#### Conditions for unblinding {17b}

Whenever a patient experiences any attributable drug side effects, her/his information will be recorded, the intervention would be stopped and necessary care will be applied. Then his/her study group will be revealed to the treating physician.

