### Data collection, management, and analysis

#### Data collection methods {18a}

Once the patient enters the study, he or she will be in touch by telephone with the study’s clinic. The clinic provides the necessary training over the phone to the patient to get acquainted with the symptoms of COVID-19. In case of suspicious symptoms or contact with a suspected patient or patient with definite COVID-19, the patient will be invited to the clinic and will be examined clinically and paraclinically (Additional file 1). Besides, all patients at each visit for cancer treatment will be evaluated by their treating physician for signs of COVID-19. If there is any clinical suspicion, the patient is referred to the clinic. The research team was invited to a coordination meeting to review the study protocol. Predictable limitations were discussed and questions were answered. The outcome assessors were trained to reduce any interobserver variations.

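### With only two shared pack codes, one side-effect reveal tells a treating physician the arm of every patient whose letter that physician knows, although treating physicians are listed as blinded

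*Protocol article*

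**What the plan says.** All references are to the protocol article.

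- **Codes.** Allocation concealment mechanism {16b} describes two kinds of pack: "groups A and B are provided to the treating physicians without specifying which is the drug or the placebo". On the envelopes it adds: "The content of each random envelop identifies patients’ group, A or B".
- **Who sees the letter.** Under Implementation {16c} the treating physician takes the envelope and "gives the corresponding pill package to the patient".
- **Reveal.** Under Conditions for unblinding {17b}, any side effect attributed to the drug leads to recording, stopping of the intervention and care. The section ends: "Then his/her study group will be revealed to the treating physician".
- **Blinding claim.** Who will be blinded? {17a} calls the trial triple-blind and states: "The intervention arm is unknown to patients, treating physicians, researchers, and analyzers".
- **Role in finding cases.** Data collection methods {18a} says that "all patients at each visit for cancer treatment will be evaluated by their treating physician for signs of COVID-19", with referral to the clinic on suspicion. Intervention description {11a} also has treating physicians refer suspicious cases, and it says that patients without symptoms are not tested by PCR.
- **Block size.** Under Sequence generation {16a}, "a random sequence is generated using quadruple blocks".

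**The concern.** A blind that rests on two shared codes fails as a whole once one code is decoded. The patient whose group is revealed matters little to the analysis. Patients with drug side effects leave the study ({11b}), no outcome data are collected after discontinuation ({18b}), and the analysis is per protocol ({20c}). The harm falls on the patients who stay in the analysis under the same physician, because their arms are now known too.

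That physician still screens these patients for COVID-19 at cancer visits and judges whether a symptom warrants referral. Without symptoms and referral there is no PCR, so a difference between arms in the readiness to refer can become a difference in observed incidence. Few events are expected, so one or two cases found or missed could change the comparison. A physician who can read the letters as treatments may also be able to anticipate some later allocations.

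**Working it through.** The protocol gives no figure on this point to reproduce. The argument rests on the text, and the arithmetic only shows scale.

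**Step 1: the sections side by side.**
1. {16b} and {16c}: the treating physician knows the letter of each patient he or she enrols.
2. {17b}: after an attributable side effect, that patient's group is revealed to the same physician. The letter is already known, so the reveal can only mean drug or placebo.
3. There are two letters and two arms. If A is the drug, B is placebo, and the reverse. One reveal in either arm decodes both.
4. {17a} lists treating physicians as blinded. After the first reveal this is untrue for that physician's patients.
5. No section describes patient-specific codes or recoding after a reveal.

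**Step 2: chance of at least one reveal.** Let q be the chance per patient of an attributable side effect and m the number of patients whose letters one physician knows. Both are assumptions, and patients are taken as independent. I use m = 60/5 = 12, that is, the 60 planned patients spread evenly over five centres with one physician each.

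P(at least one reveal) = 1 − (1 − q)^m

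| q | m = 12 | m = 60 |
|---|---|---|
| 1% | 1 − 0.99^12 = 11.4% | 45.3% |
| 2% | 1 − 0.98^12 = 21.5% | 70.2% |
| 5% | 1 − 0.95^12 = 46.0% | 95.4% |
| 10% | 1 − 0.90^12 = 71.8% | 99.8% |

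The m = 60 column applies only if the meaning of the letters is shared across all centres, which the protocol does not say.

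**Step 3: comparison with unique codes.** With one code per patient, the expected share of patients whose arm becomes known is q itself. At q = 5% and m = 12 that is 5%, against 46% with shared letters.

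**Step 4: later allocations.** In a block of four with two of each letter there are 6 orderings.
- Two of them (AABB, BBAA) leave the last 2 positions certain; the other four leave the last 1 certain. The average is (2×2 + 4×1)/6 = 1.33 of 4 positions, or 33%.
- The best guess is right with probability 1/2, 2/3, 2/3 and 1 at the four positions. The average is 2.833/4 = 70.8%.

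These figures hold only for a physician who knows the block size, knows where blocks start and sees every consecutive letter. They become predictions of treatment only after a reveal.

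**Step 5: events at stake.** Sample size {14} cites an incidence of 1 to 8%. For 30 patients per arm that is 0.3 to 2.4 cases, or 0.6 to 4.8 in 60 patients, before any drug effect.

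**The case against.** The strongest case on the other side concerns reach, and most of it stands.

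- **Not every patient in the trial.** A reader might infer that one reveal unblinds the whole trial. The text supports this only for patients whose letter that physician knows. Nothing says that a decoded letter travels between the two hospitals and three clinics.
- **Not every blinded party.** A reader might also infer that the triple-blind claim fails altogether. {17b} reveals the group to the treating physician alone. Patients, the clinic physician and the analyst are not unblinded by the text. The clinic physician also manages side effects ({5d}), so knowledge could spread to the person who evaluates COVID-19, but no section says that it does.
- **Not the only route to work-up.** Patients are taught the symptoms and go to the clinic themselves ({11a}). They are in telephone contact and are invited in for symptoms or exposure ({18a}). The data monitoring committee also refers patients ({21a}). The diagnosis is made at the dedicated clinic with PCR, so the clinical part of the case definition is not in the treating physician's hands.
- **Timing.** A reveal cannot affect patients who have already completed their 10 weeks of monitoring, and by the dates in {15} recruitment ran for about eight months. The chance of a reveal is therefore not a measure of bias.
- **Blocks.** An epidemiologist generates the list. The protocol does not say whether physicians know the block size or whether there is one list or one per centre. With a single list over five centres, a physician would not normally see complete blocks.

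These points narrow the consequence. They do not remove the conflict between {17a} and {17b} for treating physicians, nor do they protect the referrals that those physicians make.

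**Conclusion.** The concern holds in a limited form. As written, {16b}, {16c} and {17b} let one reveal decode the arm of every past and future patient whose letter the physician knows. This contradicts {17a} for treating physicians only.

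The likely effect is possible bias in one of several referral routes. There is also weaker concealment for later patients, if the physician knows the block size and sees consecutive letters.

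The size is uncertain. With an assumed 12 patients per physician, the chance of at least one reveal runs from about 11% at a 1% side-effect rate to 72% at 10%. The higher figures for 60 patients, 70% at 2% and 95% at 5%, require that the code's meaning be shared across all centres, and they should not be quoted without that condition. None of these figures estimates the bias in the result, and the documents do not show that any reveal took place.

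**What to change.** **Design.** Put a unique kit number, not A or B, in each envelope and on each pack, so that a reveal exposes one patient only. Route each reveal through the clinician outside the research team who already holds the allocation ({5d}), and log its date and recipient. Reconcile {17a} with {17b}. Which clinical events should lead to a reveal is for the trial team to settle. The cost is relabelling of packs and a paragraph across {16b} and {17b}.

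**This trial.** Recruitment is over, so relabelling can only serve as a lesson for later trials. What can still be done:
1. Report the number and dates of reveals for each treating physician, including none if that is the case.
2. Qualify the triple-blind claim: treating physicians were blinded only up to their first reveal.
3. Add a sensitivity analysis of the primary endpoint in which both follow-up and cases of each physician's patients are censored at that physician's first reveal. Dropping later cases while keeping the full denominators would give wrong incidences. Incidence should therefore be taken over the time actually at risk, and patients enrolled after the reveal contribute nothing.
4. State that this analysis will be imprecise. At most 0.6 to 4.8 cases are expected in 60 patients at the cited incidence, and fewer after censoring.

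The cost is a log compiled from existing records and one additional analysis.
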